**Methods:**

In a randomized controlled trial, we will compare blended therapy and face-to-face therapy in routine care. We intend to randomize 1152 patients nested in 231 psychotherapists in a 1:1 ratio. Patients in the blended therapy group will receive access to a **t**herapeutic **on**line **i**ntervention (TONI). TONI contains 12 transdiagnostic online modules suited for psychodynamic, cognitive behavioral, and systemic therapy. Psychotherapists decide which modules to assign and how to integrate TONI components into the psychotherapeutic process to tailor treatment to their patients’ specific needs. We will assess patients at baseline, 6 weeks, 12 weeks, and 6 months. Patients enrolled early in the trial will also complete assessments at 12 months. The primary outcomes are depression and anxiety at 6-month post-randomization, as measured by PHQ-8 and GAD-7. The secondary outcomes include satisfaction with life, level of functioning, personality traits and functioning, eating pathology, sexual problems, alcohol/drug use, satisfaction with treatment, negative effects, and mental health care utilization. In addition, we will collect several potential moderators and mediators, including therapeutic alliance, agency, and self-efficacy. Psychotherapists will also report on changes in symptom severity and therapeutic alliance. Qualitative interviews with psychotherapists and patients will shed light on the barriers and benefits of the blended intervention. Furthermore, we will assess significant others of enrolled patients in a sub-study.

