#### Sample size {14}

The sample size calculation is based on a clinically relevant additive effect with an effect size of *d* = 0.2 in favor of blended therapy [20, 21]. To detect this effect in a randomized controlled trial with a t-test (alpha error level = 5%, two-sided) for independent samples at 6 months post-randomization with a power of 80 percent requires 400 subjects per treatment group. Randomization occurs at the patient level, but patients are simultaneously nested in therapists. With an average of 25 new treatment cases per psychotherapist per year [22], we conservatively assume that an estimated minimum of 5 patients per psychotherapist agree to participate in the trial. To adequately address nesting, the therapist effect must be considered. Based on recent studies, we assume an intraclass correlation of 0.05 [23]. This results in a design effect of 1.2 [design effect = 1 + (*n*_*C*_ − 1) × ICC = 1 + (5 − 1) × 0.05 = 1.20]. Additionally, we estimate that 20% of patients will drop out of the study by the time of the post-treatment assessment [24]. Considering these factors results in a required sample of at least (400 × design effect × missing values = 400 × 1.2 × 1.2) 1152 patients (~ 231 psychotherapists).

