##### Secondary outcome measures

All secondary outcome measures (see Table 2) have shown satisfactory reliability and validity in previous studies. We will assess satisfaction with life with the 5-item Satisfaction with Life Scale (SWLS) [31, 32]. Physical and psychosocial functioning will be assessed with the 35-item Assessment of Quality of Life (AQoL-8D) [33]. For transdiagnostic symptoms, we will assess issues relating to eating/body image with the 8-item EDE-Q8 [34], alcohol and cannabis use with the 3-item AUDIT-C [35] and 4-item DUDIT-C [36], and sexual functioning with the 5-item Massachusetts General Hospital Sexual Functioning Questionnaire (MGH) [37]. Personality traits will be assessed with a brief version of the Personality Inventory for DSM-5 (PID5BF +) [38] and personality structure with the OPD-Structure Questionnaire Short form [39]. We will assess satisfaction with treatment with an adapted version of the 8-item Client Satisfaction Questionnaire (CSQ-8) [40, 41] and negative effects with the 20-item Negative Effects Questionnaire (NEQ) rated both by patients as well as psychotherapists [42]. Patients will also report their health care utilization with selected items of the FIMPsy [43]. Psychotherapists will rate symptoms and changes in general symptomatology using the CGI-S and CGI-C [44]. Patients and psychotherapists will rate the usability of the blended intervention with the 10-item System Usability Scale (SUS) [45]. At *t*_3_, psychotherapists will be asked to quantify the time they spent working with the online modules per month. They will also report in open-ended questions which potentials and limitations they see in applying blended care and how TONI can be improved.

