## Statistical methods

### Statistical methods for primary and secondary outcomes {20a}

For the primary analyses, we will include data of all randomized patients (intention-to-treat (ITT) analysis). To account for the nesting of patients (level 1) in psychotherapists (level 2), the ITT effect is estimated 6 months after the start of treatment using multilevel models. In an exploratory analysis, the influence of the actual use of the online modules is analyzed. For this purpose, the extent of actual use (e.g., number of modules used) and the time of use are inserted as moderators, and conditional effects are estimated. The same analyses are repeated for the secondary outcome measures. An appropriate alpha error correction is applied to avoid alpha error accumulation for secondary outcomes (Bonferroni-Holm). Effect sizes for pre- to post-treatment and between-group comparisons for the main and secondary outcomes will be calculated to evaluate the effectiveness of the intervention. The qualitative interviews will be recorded, transcribed, and analyzed according to a qualitative content analysis by trained staff with an appropriate review of the assessment quality (inter-rater reliability).

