#### Composition of the data monitoring committee, its role, and reporting structure {21a}

A data monitoring committee is not planned for this trial. Instead, all patients are enrolled in psychotherapy in routine care, all data will be coded directly to the system where no adjustments can be made to data, and all actions are logged.

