#### Adverse event reporting and harms {22}

During the trial, all patients are enrolled in outpatient therapy in routine care. In case of adverse events, psychotherapists will attend to the adverse events and take appropriate measures to alleviate them. At post-assessment, we will collect the negative effects caused by the treatment systematically, as suggested by Rozental and colleagues [56]. Participants — psychotherapists, patients, and their significant other — will complete the NEQ and are encouraged to further note all adverse events that occurred during treatment in an open-ended question. In addition, other markers indicative of adverse events, like hospitalization, as assessed by FIMPsy, and deterioration rates, will be published.

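### The Bonferroni-Holm rule for secondary outcomes does not exempt negative effects (NEQ), so a formal finding of harm has to share its error level with the efficacy scales

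*Protocol article*

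**What the plan says.** Four places in the protocol article have to be read together.

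- **Statistical methods for primary and secondary outcomes {20a}.** After describing the intention-to-treat multilevel analysis, the article says "The same analyses are repeated for the secondary outcome measures" and then "An appropriate alpha error correction is applied to avoid alpha error accumulation for secondary outcomes (Bonferroni-Holm". It does not enumerate the family and names no exception.
- **Secondary outcome measures.** The list includes "negative effects with the 20-item Negative Effects Questionnaire (NEQ) rated both by patients as well as psychotherapists".
- **Abstract, Methods.** The secondary outcomes end with "satisfaction with treatment, negative effects, and mental health care utilization".
- **Adverse event reporting and harms {22}.** "At post-assessment, we will collect the negative effects caused by the treatment systematically"; the instrument is again the NEQ, completed by patients, psychotherapists and significant others, with an open-ended question on adverse events. The section adds that "other markers indicative of adverse events, like hospitalization, as assessed by FIMPsy, and deterioration rates, will be published". It gives no separate test, error level or exemption for harms.

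Table 2 schedules the NEQ once, at t3.

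**The concern.** A familywise correction on efficacy scales guards against claiming a benefit that is not there. On a harm scale the same correction guards against declaring a harm, and the costly error there is usually a missed one. A Holm-adjusted p-value is never smaller than the raw one, so the direction is the same for any family of two or more.

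Under Holm the threshold that the NEQ must meet also depends on how many efficacy scales happen to be significant, which has no safety rationale. At stake is the formal conclusion: a real excess of negative effects in the blended arm could be labelled not significant because the error level was shared with scales for life satisfaction, eating pathology, personality and so on.

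**Working it through.** **Inputs from the article** (Sample size {14} and Implementation {16c}): d = 0.2; "alpha error level = 5%, two-sided"; power 80%; 400 per arm before inflation; design effect 1.2; dropout 20%; total 1152; 1:1 allocation.

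**Assumptions, because the article gives no figure:** the family size m, and the size of an NEQ excess. I use 0.2 SD, which is the plan's efficacy effect and not a documented harm effect.

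**1. The plan's own figure.** A two-sample t-test with d = 0.2, two-sided 5% and 80% power needs 393.4 per arm, which the article gives as 400. Then 2 × 400 × 1.2 × 1.2 = 1152, and 1152 / 5 = 230.4, about 231 therapists. The figure reproduces.

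**2. Patients analysed.** 1152 × 0.8 / 2 = 460.8 per arm (461). Dividing by the design effect, 460.8 / 1.2 = 384 effective per arm. Both are carried through.

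**3. Family size.** Between-arm measures named under Secondary outcome measures: SWLS, AQoL-8D, EDE-Q8, AUDIT-C, DUDIT-C, MGH, PID5BF+, OPD short form, CSQ-8, NEQ (patient), NEQ (therapist), FIMPsy, CGI-S and CGI-C. That is 14, or 13 if the two NEQ raters count once. The SUS is left out because it rates the blended intervention only.

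**4. Unadjusted test and first Holm step.** Noncentral t power; the first step uses 0.05 / m, so 0.05 / 14 = 0.0036.

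| NEQ excess | Test level | 384 per arm | 461 per arm |
|---|---|---|---|
| 0.2 SD | 0.05 | 79% | 86% |
| 0.2 SD | 0.05 / 10 | 48% | 59% |
| 0.2 SD | 0.05 / 14 | 44% | 55% |
| 0.2 SD | 0.05 / 20 | 40% | 50% |
| 0.15 SD | 0.05 | 55% | 62% |
| 0.15 SD | 0.05 / 14 | 20% | 26% |

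**5. Full Holm procedure.** The first step is the strictest. Once other outcomes are rejected, the NEQ threshold relaxes towards 0.05. I simulated 14 normal test statistics with mean d / √(2/n), correlation 0 or 0.4, and 200,000 replicates per scenario. The NEQ has d = 0.2 throughout.

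| Other 13 outcomes | 384 per arm | 461 per arm |
|---|---|---|
| All null | 44% | 55% |
| All d = 0.1 | 45% | 56% |
| All d = 0.2 | 54–55% | 67–68% |

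**6. Loss against the unadjusted test.** The largest is 79 − 44 = 35 percentage points and the smallest is 86 − 68 = 18.

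**The case against.** The best defence is that the article never says the correction covers all secondary outcomes. It speaks of an appropriate correction for secondary outcomes, and which scales, raters and time points form the family is commonly settled in the analysis plan, which is not shown. It also ties the between-group effect sizes to evaluating effectiveness and gives harms a section of their own, so an efficacy-only family is possible. This stands in part: that every secondary outcome is in the family is an inference. But the article does name the method and its target, places the NEQ within that target, and exempts nothing. That is a stated rule and not a missing detail.

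Three stronger readings are tempting and are not supported.

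- **That the plan hides harm.** Holm changes no effect size, and between-group effect sizes are promised for the secondary outcomes. Open-ended adverse event reports are collected, and deterioration and hospitalisation rates will be published with no correction attached. Only the formal verdict on the NEQ is affected.
- **That the missing oversight body makes it worse.** The article says "A data monitoring committee is not planned for this trial". Such a committee works during the trial; its absence has no bearing on how final p-values are adjusted.
- **That the NEQ is always tested at 0.05 / 14.** Holm is step-down, so this is the floor, and the range in the second table is the fair statement.

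One further objection stands in full. The NEQ comparison is two-sided. Simply taking it out of the family would also allow an uncorrected claim that blended therapy causes fewer negative effects, so the repair needs a limit.

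**Conclusion.** The point holds as a cheap improvement. As written, the plan corrects secondary outcomes by Bonferroni-Holm, counts the NEQ among them, uses the NEQ as its systematic harms instrument, and exempts it nowhere. The direction of the effect is certain for any family of two or more. The size rests on two assumptions, 14 measures in the family and a 0.2 SD excess. On these, power to declare the excess falls from 79–86% to 44–55% if the other outcomes are null, and to 54–68% if all have d = 0.2. The consequence is confined to the formal significance statement on negative effects. If the analysis plan already limits the family to efficacy outcomes, a sentence in the article saying so closes the point.

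**What to change.** In Statistical methods for primary and secondary outcomes {20a}, state that:

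1. the Bonferroni-Holm family holds the efficacy secondary outcomes only;
2. the NEQ (patient and therapist), deterioration rates and hospitalisation from FIMPsy are reported by arm with unadjusted 95% confidence intervals, as harm signals;
3. the other FIMPsy utilisation items stay in the family;
4. no uncorrected claim of benefit, meaning fewer negative effects, is drawn from the NEQ.

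Add a cross-reference in Adverse event reporting and harms {22}. No data collection or sample size changes.

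The cost is about a 5% chance of a false signal per harm measure. For the four measures in item 2, if they were independent, the chance of at least one would be 1 − 0.95⁴ = 18.5%, which is why they should be read as signals and not as proof. There is a small gain as well: with the two NEQ ratings removed, the first Holm step for the remaining 12 measures moves from 0.05 / 14 = 0.0036 to 0.05 / 12 = 0.0042.

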### Interim analyses {21b}

No interim analysis is planned in this trial.

### Methods for additional analyses (e.g., subgroup analyses) {20b}

Moderator and mediator analyses will be conducted at a later stage (subsequent to the main outcome paper) to analyze whether certain factors predict the differential effects of the interventions or mediate treatment effects.

### Methods in analysis to handle protocol non-adherence and any statistical methods to handle missing data {20c}

We will estimate the ITT effect, which is the effect of treatment assignment. This allows us to evaluate the effect of such an assignment (regardless of whether it is followed or not). For the primary analyses, missing values are multiply imputed or estimated using full information maximum likelihood, depending on the variables for which missing values occur. Both procedures are considered gold standards in dealing with missing values for which the missing at random (MAR) assumption applies. Additional covariates are considered to make the MAR assumption plausible and increase the precision of the effect estimates.

### Plans to give access to the full protocol, participant-level data, and statistical code {31c}

De-identified participant-level data as well as analysis code will be made publicly available through a research repository (OSF).

### Oversight and monitoring

#### Composition of the coordinating center and trial steering committee {5d}

There is no independent Trial Steering Committee. Instead, the research team reviews recruitment rates weekly and meets on a monthly basis to discuss key milestones as well as the conduct the research, ensuring the integrity of the protocol and conduct of the study. Any significant amendments to the study protocol will be provided to and approved by the ethics committee of Psychologische Hochschule Berlin before implementation.

#### Composition of the data monitoring committee, its role, and reporting structure {21a}

A data monitoring committee is not planned for this trial. Instead, all patients are enrolled in psychotherapy in routine care, all data will be coded directly to the system where no adjustments can be made to data, and all actions are logged.

#### Adverse event reporting and harms {22}

During the trial, all patients are enrolled in outpatient therapy in routine care. In case of adverse events, psychotherapists will attend to the adverse events and take appropriate measures to alleviate them. At post-assessment, we will collect the negative effects caused by the treatment systematically, as suggested by Rozental and colleagues [56]. Participants — psychotherapists, patients, and their significant other — will complete the NEQ and are encouraged to further note all adverse events that occurred during treatment in an open-ended question. In addition, other markers indicative of adverse events, like hospitalization, as assessed by FIMPsy, and deterioration rates, will be published.

#### Frequency and plans for auditing trial conduct {23}

Psychologische Hochschule Berlin does not have a dedicated research audit department. The research team meets monthly to review trial conduct.

#### Plans for communicating important protocol amendments to relevant parties (e.g., trial participants, ethical committees) {25}

Any amendments to the study protocol would have to be approved first by Psychologische Hochschule Berlin’s ethics committee. If approved, these changes would have to be reported in the trial register. Finally, any amendments would be reported in the trial paper.

#### Dissemination plans {31a}

The trial results will be published in a peer-reviewed journal. The results will also be presented at scientific conferences. A popular science summary of the results will be posted online for laymen and study participants. An anonymized data set as well as statistical code used to analyze the data will be published in a data repository on OSF.

## Discussion

This is the first RCT to investigate a transdiagnostic and transtherapeutical as well as modular blended intervention in German psychotherapy in routine care. Unique to this intervention, TONI will be the first Internet-based intervention to cover therapeutic principles across cognitive -behavioral, psychodynamic, and systemic therapy. The majority of transdiagnostic Internet-based interventions focus on anxiety and depression. However, this focus neglects other issues of the internalizing and the whole externalizing spectrum of pathology. TONI taps into this, with modules corresponding to transdiagnostic processes and principles across the whole spectrum of mental health. If the blended therapy’s effectiveness and utility are demonstrated, TONI can be a useful and promising tool for psychotherapists with different theoretical backgrounds and for a wide range of patients. The modular and flexible structure of TONI allows psychotherapists to tailor the blended treatment to their and their patients’ needs, making it suitable for real-life settings.

Our results will highlight whether integrating digital tools into psychotherapy has a positive impact. Importantly, this trial will be sufficiently powered to detect small differences between blended and face-to-face therapy to better understand blended therapy’s potential in terms of effectiveness. To be reflective of the broad inclusion criteria, transdiagnostic spectra and symptoms will be included to capture changes beyond anxiety and depression. Besides effectiveness rates, other markers are important determinants of interventions’ feasibility and dissemination potential. We will cover this broadly, assessing satisfaction with treatment and negative effects and qualitatively interviewing patients and psychotherapists. Our results will shed light on how psychotherapists and patients use digital tools and the advantages and disadvantages of such an integration. Notably — since there is a lack of research on how Internet-based interventions and psychotherapy should be blended — we will investigate whether the degree of integration of online interventions in psychotherapy matters and to what extent. In addition, our findings will contribute to knowledge on which patients benefit from blended therapy and which underlying mechanisms mediate effects.

The trial has several limitations: This study compares two active treatments, hypothesizing that blended therapy may be superior to regular psychotherapy in routine care. One of the assumptions behind this hypothesis is that patients may receive a higher treatment dosage by using additional online modules. However, the treatment dosage is dependent on whether psychotherapists actively engage with the intervention and assign modules. A strength of this is that it represents real-world behavior and as such is externally more valid. However, it may limit conclusions about the actual effect of making use of the full potential of the modules. We collect data on the usage of the modules and will add it as moderators to evaluate its possible impact on the results. Psychotherapists will also be in charge of recruiting their patients. This may constitute a bottleneck for the recruitment of patients, potentially jeopardizing recruitment rates. The recruitment procedure may limit the generalizability of the results, as psychotherapists choose which patients to invite to participate in the study. In addition, we are not conducting a cost analysis.

The present RCT investigates the superiority of blended over psychotherapy alone in routine care. The integration of online interventions like TONI that use a common therapeutic language and address therapeutic principles shared across therapeutic approaches has the potential to advance the effectiveness of psychotherapy. TONI may not only improve the effectiveness of psychotherapy in routine care but help save therapists’ resources and close treatment gaps.

## Trial status

Psychotherapist and patient recruitment commenced in mid-June 2022 and is expected to be completed by June 2023.

## Data Availability

After the publication of the trial results, a de-identified data set as well as analysis code will be made publicly available on the research data repository OSF.

## Abbreviations

ACE: Adverse Childhood Experiences Questionnaire
AQoL-8D: Assessment of Quality of Life
ASKU: General Self-efficacy Short Scale (Allgemeine Selbstwirksamkeit Kurzskala)
AUDIT-C: Alcohol Use Disorders Identification Test-Concise
DUDIT: Drug Use Disorder Identification Test
CBT: Cognitive behavioral therapy
CGI-C: Clinical Global Impression-Change
CGI-S: Clinical Global Impression-Scale
CONSORT: Consolidated Standards of Reporting Trials
CPPS: Comparative Psychotherapy Process Scale
CSQ-8: Client Satisfaction Questionnaire
DRKS: Deutsches Register Klinischer Studien (German Register of Clinical Trials)
EDE-Q8: Eating Disorder Examination-Questionnaire 8
FIMpsy: Questionnaire of Medical and Non-Medical Health Care Utalization by Mental Disorders (Fragebogen zur Inanspruchnahme medizinischer und nicht medizinischer Versorgungsleistungen bei psychischen Erkrankungen)
GAD-7: Generalized Anxiety Screener 7
GBA: Gemeinsamer Bundesausschuss
IEQ: Involvement Evaluation Questionnaire
ITT: Intention-to-treat
MAR: Missing at random
MGH: Massachusetts General Hospital Sexual Functioning Questionnaire
MHSES: Mental Health Self Efficacy-Scale
MULTI: Multitheoretical List of Therapeutic Interventions
NEQ: Negative Effects Questionnaire
OPD: Operationalized Psychodynamic Diagnostic (Operationalisierte Psychodynamische Diagnostik)
ORS: Outcome Rating Scale
OSF: Open Science Framework
PHQ-ADS: Patient Health Questionnaire Anxiety and Depression Scale
PHQ-4/8/9: (4/8/9-item) Patient Health Questionnaire
PID-5-BF +: Personality Inventory for DSM-5 Brief Form
PsyTOM: Psychotherapy through blended therapy with transdiagnostic online modules
RCT: Randomized controlled trial
SPIRIT: Standard Protocol Items: Recommendations for Interventional Trials
SRS: Session Rating Scale
SUS: System Usability Scale
SWLS: Satisfaction with Life Scale
TAI: Therapeutic Agency Inventory
TONI: Therapeutic online intervention
WAI-SR: Working Alliance Inventory-Short Revised
